## Abstract

**Background:**

Despite recommendations for monitoring patients with chronic and high-risk conditions, gaps still remain. These gaps are exacerbated in outpatient care, where patients and clinicians face challenges related to care coordination, multiple electronic health records, and extensive follow-up. In addition, low-income and racial/ethnic minority populations that are disproportionately cared for in safety net settings are particularly at risk to lapses in monitoring.

**Methods:**

We aim to implement and evaluate a health information technology platform developed using systems engineering methodologies. The implementation is situated in a clinic that monitors patients with head and neck cancer within a large, urban, publicly funded hospital. Our study will evaluate the time it takes for patients to progress through key treatment milestones prior to and after implementation of the tool. We will use models controlling for secular trend to estimate the effect of the tool on improving timely and successful completion of guideline-based care processes.

**Discussion:**

This protocol details the evaluation of the effectiveness of a human-centered health information technology intervention on improving timely delivery of care for high-risk populations. Other settings, including those that face challenges related to limited resources to devote to safety programs and fragmented health information technology, may benefit from this approach.

**Trial registration:**

ClinicalTrials.gov, NCT03546322. “Customized Registry Tool for Tracking Adherence to Clinical Guidelines for Head and Neck Cancers.” Registered 1 June 2018.

## Background

Since the publication of “To Err is Human” and other subsequent reports by the Institute of Medicine, there has been increasing focus on harms caused by medical care [1–3]. Errors of omission, or failing to deliver needed treatment, are especially common in the ambulatory setting, where patients receive only 55% of recommended preventive care. Those with chronic conditions fare no better, receiving only 56% of recommended care [4].

Delivery of appropriate care in the ambulatory setting frequently requires monitoring and treatment over multiple visits and often extended periods of time, particularly for those with chronic diseases or complex conditions. Missed monitoring may put patients at high-risk of adverse effects of treatment or failed detection of progression of disease. In addition to periodic monitoring, patients with complex conditions may require coordination between multiple specialties and complex treatment regimens that require timely completion of needed steps. For example, patients with cancer often require extensive diagnostic workup, evaluation by an interdisciplinary group of providers, and coordination of multiple treatment modalities. In head and neck cancer, the National Comprehensive Cancer Network (NCCN) has published guidelines for recommended pre-treatment workup, treatment, and post-treatment monitoring [5]. Despite the presence of these guidelines, fewer than half of patients undergoing surgery for head and neck squamous cell carcinoma receive post-surgery radiation within the timeframe recommended by NCCN guidelines [6]. Unsurprisingly, studies show an association between delays in treatment initiation and increased mortality [7]. Treatment interruptions have also been associated with both persistent disease [8] and mortality [9]. Perhaps more concerning, the proportion of patients receiving guideline-based care has decreased over time, and patients with lower socioeconomic status who receive care regardless of insurance status or their ability to pay in safety net settings appear to be most vulnerable [6, 10]. Though reasons for failure to adhere to guidelines are complex, lapses are frequently the result of the inability of clinics and health systems to proactively identify patients who meet criteria for guideline-based diagnostic or therapeutic interventions [11].

Traditionally, face-to-face visits have been the primary means of monitoring patients and ensuring completion of treatment steps. However, given the frequency of errors of omission—missed cancer diagnoses constitute the leading cause of paid medical malpractice claims among outpatients—solutions to systematically identify upcoming and overdue monitoring across a population of patients are needed [12, 13]. Similar to cancer screening, which is now often based on electronic registries and outreach to patients rather than purely visit-based activity, there is an opportunity to use technology and team-based workflows to enhance outpatient monitoring for high-risk conditions.

As part of the process for developing the information technology (IT) tool used in this study, we conducted a series of qualitative interviews with practitioners in a number of clinics involved in delivering care to patients with chronic or complex medical conditions at high-risk of experiencing monitoring related medical errors. We applied a technique known as journey mapping to map the process of patient monitoring in each clinic and identify difficult or high-risk steps in the monitoring process [14]. Focusing on “pain points” identified through the journey mapping process for the Otolaryngology Clinic at the Zuckerberg San Francisco General Hospital, we applied a framework adapted from Systems Engineering Initiative for Patient Safety (SEIPS) [15] toward the development of a health IT tool that allows for context-specific customization of monitoring and treatment protocols for patients with head and neck cancer. This tool enables the clinic to develop custom diagnostic and treatment plans for patients with head and neck cancer, and facilitates subsequent population level tracking of completion of needed diagnostic or treatment steps.

We aim to implement the tool developed through this journey mapping process in the head and neck cancer clinic within a large safety net hospital and evaluate impact of this tool on timeliness of diagnostic evaluation, treatment initiation, and monitoring, as well as adherence to established protocols. Our objective here is to describe the study protocol for this pilot evaluation.

## Methods

### Study design

This study will evaluate implementation of a health IT tool designed to track patient progress toward diagnostic evaluation, treatment, and post-treatment monitoring for head and neck cancer. The study will evaluate the amount of time it takes patients to progress through key treatment milestones prior to and after implementation of the tool. The study design is a cohort study consisting of two cohorts of patients—a pre-treatment cohort including patients who have received a diagnosis of head and neck cancer but have not started treatment, and a post-treatment cohort of patients who have initiated treatment. Models controlling for secular trend will be used for data analysis to estimate the effect of tool implementation on improving timely and successful completion of guideline-based care processes. This analytic approach will help separate out the effect of the intervention from other temporal trends in care process completion. This study was approved by the University of California, San Francisco Institutional Review Board (12-09658) and is registered on ClinicalTrials.gov (Protocol ID: P30HS023558-1).

### Clinical setting

This study will take place within the Otolaryngology-Head and Neck Surgery Clinic at the Zuckerberg San Francisco General Hospital, a large county hospital affiliated with a tertiary care academic center. Patients served by this clinic are publicly insured. While the clinic has used an electronic health record for 22 years, it faces challenges, shared by many safety net systems, associated with coordinating care across multiple electronic platforms and record-keeping systems. Until adoption of this tool, the clinic did not have access to an integrated electronic registry system to monitor progress of care plans for patients undergoing diagnostic workup or treatment for head and neck cancers.

### Health IT tool

The intervention evaluated in this study is an innovative workflow that incorporates an electronic registry tool. The tool integrates data from several, fragmented electronic medical records and allows clinic staff to monitor patient progress through care plans across the clinic’s entire panel (Fig. 1). Prior to development of this tool, the clinic relied on tracking methods requiring intensive manual data entry to populate a database that was not integrated with the medical record. These methods included a system of paper note cards and later an electronic spreadsheet to track patient progress. Using this tool requires changes in the clinic team’s workflow and communication.

**Fig. 1 Fig1:**
[figure not shown]
The health IT tool integrates data from three separate HL7 data sources representing registration, lab, and radiology data into a single database

The tool evaluated here was developed to address key process challenges identified through a “journey mapping” method with clinic staff in five clinics that monitor high-risk cancer situations: otolaryngology, pulmonary, breast, urology, and gastroenterology [14]. The journey mapping process identified two vulnerabilities present across all five sub-specialty clinics studied, namely (1) the need to track patient progress toward diagnostic or therapeutic goals and (2) the difficulty in creating comprehensive patient lists for monitoring. Practitioners in the Otolaryngology-Head and Neck Surgery Clinic also identified challenges related to coordinating multi-specialty treatment plans. Our team mapped processes identified during the journey mapping exercise onto the SEIPS model for work system, a model that describes the interrelated components of people, tasks, technology/tools, organization, and environment that make up clinical work systems [15]. We chose to focus on developing a solution to address challenges in work systems related to tasks and technology, as these were both the most clear areas of challenge and the most immediately amenable to change in the Otolaryngology-Head and Neck Surgery Clinic. In collaboration with CipherHealth, a health IT company, we developed a registry tool that integrates clinical data from multiple electronic health records. This tool allows for creation of clinic-specific treatment plans (Fig. 2) and tailored queries to identify patients who are overdue for completing key steps of their assigned treatment plan (Fig. 3).

**Fig. 2 Fig2:**
[figure not shown]
A screenshot depicting one of the clinic-specific treatment plans co-designed with the Otolaryngology-Head and Neck Surgery Clinic. After assigning a patient to this plan, care providers will be automatically prompted to complete its associated tasks, such as ordering post-treatment imaging for a patient two months after enrollment

**Fig. 3 Fig3:**
[figure not shown]
A screenshot of the health IT tool’s panel management functionality. Users can run queries to prioritize patients overdue for key steps of their assigned monitoring plan. Patient names are fictitious for demonstration purposes

### Chart review

Chart review will be conducted for all patients in the Otolaryngology-Head and Neck Surgery Clinic undergoing diagnostic workup, treatment, or post-treatment monitoring for head and neck cancer for the 2-year period leading up to implementation of the tool and the 2-year period after the tool has been implemented (with the 6 months prior to tool implementation excluded to avoid misclassification of exposure to the intervention, as discussed below). All patients with confirmed diagnosis of head and neck cancer who were seen in the clinic at least once will be included in the chart review. Based on prior clinic chart review, there are about 75 patients with head and neck cancer seen in the clinic each year who meet enrollment criteria. Thus, the chosen 4-year time period was selected to allow for inclusion of approximately 300 patients in our sample. Data will be extracted from patient charts and will include patient demographic factors, details of the diagnosis, and key treatment dates (Table 1). Unless noted, all clinical data will be collected from the medical record for both the intervention and control time periods, to minimize differential data collection methods that may influence comparisons.

**Table 1 Tab1:** Data elements collected in chart review

Phase/data type	Data element
General: demographics	Gender
	Race/ethnicity
	Primary language
	Insurance status
General: social characteristics	Smoking status
	History of alcohol use
	History of other substance abuse
	History of homelessness/being marginally housed
	Comorbidities
	History of HIV/AIDS
General: utilization	Otolaryngology-Head and Neck Surgery visit dates and status (attended/canceled/no-show/scheduled)
	Medical oncology visit dates and status (attended/canceled/no-show/scheduled)
	Radiation oncology visit dates and status (attended/canceled/no-show/scheduled)
	Patient only seen for hospitalization
	Most recent visit date
General: outcomes	Overall follow-up time
	Survival
General: results	Imaging for cancer monitoring
	All imaging
	Thyroid-stimulating hormone test dates and results
	All lab test dates and results
	Pathology dates and results
1. Workup and treatment planning	Date of diagnosis
	Date of referral to tumor board
	Date of presentation at tumor board
	Date imaging appointments sent, scheduled, and completed
	Date referrals sent, scheduled, and completed
	TNM staging
	Site
	Histology
	P16 test results*
	Treatment plan
	Dates of patient outreach^†^
	Date of recurrence
2. In treatment	Date of dental evaluation
	Date of treatment start
	Date of treatment completion
	Recommended and received dose and treatment sessions
	Treatment result (e.g., completed, not completed, delays)
	Dates of treatment delays/complications
	Type of treatment delays/complications
	Dates post-treatment imaging ordered and completed
	Dates of patient outreach^†^

*P16 immunohistochemistry tests are recommended for newly diagnosed oropharyngeal squamous cell carcinomas

^†^Supplemental data collected from health IT tool to describe implementation of the tool, all other data collected from chart review

### Outcomes

Patients included in the study will be divided into two separate cohorts. The pre-treatment cohort will include patients with a confirmed diagnosis of head and neck cancer but who have not yet initiated treatment. The post-treatment cohort will include patients who have initiated treatment and are undergoing additional treatment modalities and monitoring. Patients who received a diagnosis of head and neck cancer and initiated any treatment will thus be present in both cohorts. Outcomes for each cohort consist of completion of key steps in the evaluation and treatment process, and are summarized in Table 2. Usual clinic protocols will be employed to address patients who are lost to follow-up (three outreach attempts, then moved to lost to follow-up list). Patients who are lost to follow-up will be included in the final analysis and will be considered to have not met the process outcome for their given cohort (i.e., it will be assumed that patients lost to follow-up from the pre-treatment cohort never initiated treatment).

**Table 2 Tab2:** Primary and secondary outcomes for each patient cohort

Cohort	Primary outcome	Secondary outcomes
Pre-treatment cohort: workup and treatment planning	- Time from diagnosis to initiation of treatment	- Time from diagnosis to presentation to tumor board - Time from diagnosis to dental evaluation - Time to first visit in medical oncology and radiation oncology clinics - Lost to follow-up (no visit for ≥ 6 months)
Post-treatment cohort: treatment	- Completion of tumor board treatment recommendations	- Lost to follow-up (no visit for ≥ 6 months) - Proportion of patients completing post-treatment radiation within 6 weeks (guideline-based treatment quality of care metric) [5, 6]

### Classification of exposure to the intervention

Patients will be considered unexposed to the intervention if they entered one of the cohorts at least six months prior to implementation of the health IT tool intervention. Patients who entered a cohort less than 6 months prior to implementation of the intervention will be excluded from that cohort. All patients entering a cohort after implementation of the tool will be considered exposed to the intervention for that cohort. For example, if a patient was diagnosed with head and neck cancer 3 months prior to implementation of the intervention and initiated treatment 1 week after implementation of the intervention, they would be excluded from the pre-treatment cohort and would be included in the post-treatment cohort and considered exposed to the intervention.

### Implementation outcomes

The key implementation outcome is feasibility. We will also measure several components of tool utilization to better understand the actor, dose, temporality, and action target of the intervention [16]. Data collection on these parameters will occur through a quarterly survey of clinic staff using the tool and through five randomly selected clinic days when the investigators will observe clinic staff and any use of the tool that occurs. The survey will ask staff to report their role in the clinic and recall for the prior week the amount of time that the tool was used, timing of use, and number of patients outreached through the use of the tool. The feasibility objective for this pilot study is to achieve consistent use throughout all clinic sessions reaching all eligible patients. The feasibility outcome which will determine success and trigger proceeding to the main trial is achievement of significant use: use during at least 80% of clinic sessions and for 80% of eligible patients.

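### The 80%/80% progression criterion is not matched by the use data described: the survey items yield neither proportion, and five observed days estimate session use too imprecisely to decide on

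*Protocol article*

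**What the plan says.** The Implementation outcomes section of the protocol article names feasibility as the key implementation outcome and attaches a decision to it: "The feasibility outcome which will determine success and trigger proceeding to the main trial is achievement of significant use", specified as "use during at least 80% of clinic sessions and for 80% of eligible patients".

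The same section describes how tool utilization is measured. The first source is a survey: "Data collection on these parameters will occur through a quarterly survey of clinic staff using the tool". Besides their role in the clinic, staff are asked to "recall for the prior week the amount of time that the tool was used, timing of use, and number of patients outreached" by means of the tool. The second source is "five randomly selected clinic days when the investigators will observe clinic staff and any use of the tool that occurs".

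Two other sections bear on the point. In the Chart review section, the footnote to Table 1 marks dates of patient outreach as "Supplemental data collected from health IT tool to describe implementation of the tool". That section also says that chart review covers every clinic patient with a confirmed diagnosis, about 75 a year, including the two years after implementation. The Minimum detectable effects section says that the sample size rests on the feasibility outcomes, that effect estimates are secondary, and that a larger trial depends on feasibility.

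**The concern.** The criterion consists of two proportions. One needs sessions with use over sessions held; the other needs patients for whom the tool was used over eligible patients. The instruments described beside it were built for something else: who uses the tool, how much, when and for what.

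The survey goes to staff who already use the tool, relies on recall of a single week, and asks for time spent, timing and a count of patients contacted. None of these items counts sessions held or eligible patients, and two staff members can report the same patient. The observed days do bear on sessions, but there are only five of them.

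At stake is the main decision that the pilot exists to inform. If the 80%/80% rule is judged on these data, a main trial could be started on a tool used well below target, or dropped although the target was met.

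**Working it through.** The protocol gives no sample size, precision or error rate for this criterion, so there is no planned figure to reproduce.

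**Step 1: what each source can supply**

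| Source in the protocol article | Session proportion | Patient proportion |
|---|---|---|
| Quarterly survey (Implementation outcomes) | No item counts sessions held or sessions with use | Count of patients contacted; no denominator; possible overlap between staff |
| Five observed days (Implementation outcomes) | Yes, from 5 days | At most the patients dealt with on those days |
| Outreach dates from the tool (Table 1 footnote) | Not stated | Approximate numerator, narrower than use |
| Chart-review list (Chart review) | No | Denominator |

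The last two rows together could approximate the patient proportion. The protocol links neither of them to the criterion.

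**Step 2: precision of five days**

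Inputs: n = 5 (Implementation outcomes). Assumption: one session per day, days independent. The exact (Clopper-Pearson) 95% limits for x of n are the 2.5% quantile of Beta(x, n − x + 1) and the 97.5% quantile of Beta(x + 1, n − x).

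- 4 of 5 (80%): 28.4% to 99.5%.
- 5 of 5: the lower limit is 0.025^(1/5) = 47.8%.

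As a range, assume two independent sessions per day, so n = 10:

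- 8 of 10: 44.4% to 97.5%.
- 10 of 10: the lower limit is 0.025^(1/10) = 69.2%.

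Even perfect use on every observed day would therefore not exclude true session use below 80%.

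**Step 3: how a decision on five days would behave**

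The protocol states no rule for the observed days. For illustration, take a pass as an observed proportion of at least 80%. For five sessions, P(pass) = 5p⁴(1 − p) + p⁵.

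- p = 0.6: 5 × 0.1296 × 0.4 + 0.0778 = 0.337.
- p = 0.8: 5 × 0.4096 × 0.2 + 0.3277 = 0.737, so failure has probability 0.263.

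| True session use | Pass with ≥4 of 5 | Pass with ≥8 of 10 |
|---|---|---|
| 60% | 0.34 | 0.17 |
| 70% | 0.53 | 0.38 |
| 80% | 0.74 | 0.68 |
| 90% | 0.92 | 0.93 |

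**Step 4: what adequate precision would take**

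With the normal approximation n = 1.96² × 0.8 × 0.2 / d², estimating a proportion near 80% to within d = 0.10 needs 3.8416 × 0.16 / 0.01 = 61.5, so 62 sessions. For d = 0.05 it needs 3.8416 × 0.16 / 0.0025 = 245.9, so 246 sessions.

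For patients, 75 a year over 2 years gives about 150 after implementation. If 120 of 150 (80%) had recorded use, the exact 95% interval would be 72.7% to 86.1%.

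**The case against.** The strongest reply is that the protocol never says that the criterion will be judged on the survey and the five days. The sentence on data collection refers to the utilization components listed just before it, and the 80%/80% rule follows with no source attached. A journal article may leave that source to a fuller document. This reading of the grammar is fair, and a reader should not take the article to state that these two instruments measure the criterion. The point survives because the criterion is itself a measure of use, the section describes use data in detail, and no other part of the article ties a better source to the rule.

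Several stronger readings are tempting and are not supported:

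- *Neither proportion can be estimated.* Too strong for sessions: randomly selected days give an unbiased estimate, provided that being observed does not change use. The fault is imprecision.
- *The patient half cannot be computed.* Also too strong: the tool's outreach dates over the chart-review list would give an approximation. It would understate use, since a patient tracked on the tool but never needing outreach would count as a non-user.
- *The decision is close to chance.* The pass probabilities rise from 0.34 at 60% use to 0.92 at 90%. That is weak discrimination; it resembles a coin toss only near 70%.
- *The survey covers 8 of 104 weeks.* This assumes four rounds a year for two years; the article gives no duration.
- *Staff are observed openly.* The article does not say so.

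It is also true that the criterion affects none of the Table 2 outcomes or their models. That limits the reach of the point, but the criterion still governs progression.

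**Conclusion.** The concern holds in this form: the protocol sets a two-part progression criterion, and the use data described alongside it do not serve that criterion. The survey items as listed yield neither proportion. The five observed days give session use with an interval running from 28% to 99.5% at an observed 80%. Under the illustrative 4-of-5 rule, true use of 60% would pass about one time in three, and true use of 80% would fail about one time in four.

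These figures assume one session per day, independence between days, and a pass mark that the protocol does not state. Two sessions per day would narrow the interval to 44% to 97.5% without changing the conclusion. Data that could support the patient half are already planned, but they are not assigned to the criterion and cover outreach only.

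**What to change.** Name the source, numerator, denominator and time window for both halves of the criterion, and base the decision on the tool's own records over the whole post-implementation period.

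- *Patients:* exposed patients with an assigned plan or recorded tool activity, over all exposed patients found by chart review.
- *Sessions:* sessions with recorded use, over all scheduled clinic sessions, provided that the tool's records are time-stamped by use.
- *Survey and observed days:* keep both as descriptive data on who uses the tool, when and how.

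The cost is a data export, matched to the clinic schedule and to the existing chart-review list. The patient half builds on an extraction already planned for outreach dates. The session half depends on the tool logging use, which the document does not confirm and which should be checked first. If it does not, session use has to be recorded in some other way on far more than five days; about 62 sessions would be needed for a margin of ±10 points.
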